#### **6.2.2. Blinding procedures**

The intervention under investigation will not be blinded however the assessment of the primary outcome at 6 months will be performed by a study team member blinded to the intervention done in the study patients.

#### **6.2.3. Other methods of minimising bias**

The use of validated scales (modified Rankin Scale, Cerebral Performance Categories ) will also allow minimizing bias.

### **6.3 Unblinding Procedures (Code break)**

Not applicable

## 7. STUDY POPULATION

### 7.1 Eligibility criteria

#### Inclusion criteria:

- In-patients aged  $\geq 18$  years, treated in an ICU or intermediate care unit
- Alteration of mental state of any etiology (i.e., primarily cerebral or not), with Glasgow-coma scale  $\leq 11$  or FOUR score  $\leq 12$ .
- Need of an EEG to exclude seizures or SE, or to evaluate prognosis as per the treating physician or the consulting neurologist.
- Informed consent obtained for research in emergency situation according to Human Research Act (HRA) art 30-31 at the time of inclusion

#### Exclusion criteria:

- Clinical and/or electrographic *status epilepticus* < 96h before randomization
- Clinical and/or electrographic seizure < 36h before randomization
- Palliative care situation, in which detection of SE or seizures would not have any impact on the patient's care.
- High likelihood of needing a surgical intervention or an invasive diagnostic procedure within the next 48 hours according to the treating physician (as this would require cEEG removal).

### 7.2 Recruitment and screening

Three hundred and fifty (350) study patients will be recruited at the participating hospital through the normal clinical practice: all adults with altered mental state needing an EEG for clinical purposes, and not presenting any exclusion criterion, will be considered.

No recruitment can be made through outpatients or advertising, for instance.

### 7.3 Assignment to study groups

The study patients will be randomized by the local investigator (or his designee) after the eligibility check and just before the intervention using the web-based secuTrial® software. The system will provide the investigator with a randomization number and intervention allocation (rEEG or cEEG).

### 7.4 Criteria for withdrawal / discontinuation of participants

Patients who during the intervention period (30-48 hours) will be diagnosed with clinical or electrical seizures or SE (10-12% are expected (Alvarez et al, Clin Neurophysiol, in press)) will exit the intervention but stay in the study and be managed according to best clinical practice. A uniform definition of electrographic seizures (minimum time >10 seconds) and SE (minimum time >5 minutes) will be used: repetitive, rhythmic or periodic discharges or spike and wave patterns occurring at a frequency of <3 Hz together with evolution in frequency, location, or with electroclinical response to anticonvulsants; or occurring at a frequency of >3 Hz. These criteria, as well as interruption of the intervention as per the treating physician will not prevent assessment of the outcomes (only analyzed as "intention to monitor", according to the intervention group allocation).

Furthermore, refusal/withdrawal of consent from the patient or representative represents a mandatory discontinuation of the study.

## 8. STUDY INTERVENTION

### 8.1 Identity of Investigational Products (treatment / medical device)

No investigational products are investigated. This study aims to compare the prognostic yield of cEEG versus rEEG interventions.

#### Experimental Intervention

Patients randomized to cEEG will be recorded with at least 21 electrodes placed according to the international 10-20 system; occasionally, a reduced montage will be allowed in patients with extensive neurosurgical scars, according to good common practice. The electrodes type and the use of automated, quantitative EEG interpretation softwares will be at the discretion of the centers, but minimal technical requirements for EEG recording in patient with troubles of consciousness as declared by the International Federation of Clinical Neurophysiology have to be fulfilled. Recordings will last a minimum of 30 and a maximum of 48 hours, in order to avoid definitive removal of electrodes during the night. During this time, one interruption to a maximum of two hours for diagnostic purposes (e.g., for neuroimaging) will be allowed. Reactivity testing using auditory and nociceptive stimuli will be performed at least twice during the recording time. Recordings will be visually interpreted by certified electroencephalographers (i.e., interpretation of the automated algorithm only won't be allowed) at least 3x during working days, and 2x during weekends and holidays, using the 2013 American Clinical neurophysiology nomenclature; interpretations will be communicated within two hours of their completion to the treating team.

#### Control Intervention

Patients randomized to rEEG will be recorded with at least 21 electrodes placed according to the international 10-20 system; occasionally, a reduced montage will be allowed in patients with extensive neurosurgical scars, according to good common practice. Recordings will last between 20 and 30 minutes; two recordings will take place over a period of 24 to 48 hours. Reactivity testing using auditory and nociceptive stimuli will be performed once per recording. Recordings will be visually interpreted by certified electroencephalographers using the 2013 American Clinical neurophysiology nomenclature, as for the experimental intervention, and the interpretation will be communicated within two hours of its completion to the treating team (idem).

#### Packaging, Labelling and Supply (re-supply)

NA

#### Storage Conditions

NA

### 8.2 Administration of experimental and control interventions

#### Experimental Intervention

EEGs are routinely needed several times a day in each participating center for seizure detection in patients with altered consciousness. The time frame of 30-48 hours for cEEG and rEEG derives from the seminal study by Claassen et al, showing that within this time lapse the vast majority of seizures are detected in critical care patients. Routine practice in the vast majority of European (and Swiss) hospital, to date, is to perform rEEG. It is also common practice to repeat rEEG in several clinical situations. Therefore, 2 rEEG were chosen as the (standard) comparator.

EEGs are routinely used in all participating centres for clinical practice. EEG interpretation will be performed by certified study team members at each site, according to current standard of clinical care; for details please see 8.1.

#### Control Intervention

Please see above 8.1.

### 8.3 Dose / Device modifications

Patients that during the intervention period (30-48 hours) will be diagnosed with clinical or electrical seizures or SE (10-12% are expected (Alvarez et al, Clin Neurophysiol, in press)) will exit the intervention and managed according to best clinical practice. A uniform definition of electrographic seizures (minimum time >10 seconds) and SE (minimum time >5 minutes) will be used: repetitive,

rhythmic or periodic discharges or spike and wave patterns occurring at a frequency of <3 Hz together with evolution in frequency, location, or with electroclinical response to anticonvulsants; or occurring at a frequency of >3 Hz. Occurrence of these criteria, as well as interruption of the intervention as per the treating physician, will not prevent assessment of the primary outcome (intention to monitor).

#### **8.4 Compliance with study intervention**

NA

#### **8.5 Data Collection and Follow-up for withdrawn participants**

If participants or representative refuse to give consent, all data collected so far will not be used. However if participants or representative withdraw consent, all data collected so far will be used for the study purposes in order not to compromise the study.

If the intervention EEG is interrupted (please see 8.3), participants will stay in the study and data will be collected at all study time points as planned but analyzed in intention to monitor.

#### **8.6 Trial specific preventive measures**

There are no preventive measures. If seizures or status epilepticus will be detected during the intervention period, the treating clinicians will manage this according to standard care.

#### **8.7 Concomitant Interventions (treatments)**

There is no restriction at all for concomitant interventions and treatment. The intervention EEG can be temporarily interrupted (in case of cEEG) to perform a diagnostic procedure, if this is acutely needed. Duration of the interruption will be reported.

#### **8.8 Study Drug / Medical Device Accountability**

NA

#### **8.9 Return or Destruction of Study Drug / Medical Device**

NA

## 9. STUDY ASSESSMENTS

### 9.1 Study flow charts

| Study period                                                                          | Screening / Inclusion | Intervention period | Follow-up |          |                 |                   |
|---------------------------------------------------------------------------------------|-----------------------|---------------------|-----------|----------|-----------------|-------------------|
| Days/Weeks/Months                                                                     | Day 1                 | Day 1-Day 2/3       | Day 3/4   | Day 7    | Week 4 (Day 29) | Month 6 (Day 180) |
| Time (hours)                                                                          | T-5 - T0              | T0 - T48            | T48 - T60 | -        | -               | -                 |
| Visit Window                                                                          | None                  | None                | + 24h     | ± 3 days | ± 4 days        | ± 10 days         |
| Assessments                                                                           |                       |                     |           |          |                 |                   |
| Demographics                                                                          | X              |                     |           |          |                 |                   |
| Admission details (time, reason, hospital service)                                    | X              |                     |           |          |                 |                   |
| Glasgow Coma Scale or FOUR score                                                      | X              |                     |           |          |                 |                   |
| Brain function alteration requiring EEG (Date, time and type)                         | X              |                     |           |          |                 |                   |
| Previous seizures                                                                     | X              |                     |           |          |                 |                   |
| Informed consent                                                                      | X              | X            | X  | X | X        | X          |
| Eligibility check and inclusion                                                       | X              |                     |           |          |                 |                   |
| Estimated body weight                                                                 | X              |                     |           |          |                 |                   |
| Charlson Comorbidity Index (CCI)                                                      | X              |                     |           |          |                 |                   |
| Modified Ranking Scale (mRS)
*extrapolated before current hospitalization   | X*             |                     |           |          | X        | X          |
| SAPS II (only if available)                                                           | X              |                     |           |          |                 |                   |
| Laboratory (only if available)                                                        | X              |                     |           |          |                 |                   |
| Randomization                                                                         | X              |                     |           |          |                 |                   |
| EEG(s) details (Dates/times, electrodes numbers, use of interpretation algorithms)    |                       | X            |           |          |                 |                   |
| Detection of seizures (time, clinical correlate) and/or SE (time, type, STRESS score) |                       | X            |           |          |                 |                   |
| Interictal epileptiform features (after ACNS)                                         |                       | X            |           |          |                 |                   |
| EEGs description                                                                      |                       | X            |           |          |                 |                   |
| Medication during EEG (except fluids, vitamins and feeding)                           |                       | X            |           |          |                 |                   |
| SAEs potentially related to EEGs                                                      |                       | X            | X  |          |                 |                   |
| Changes in clinical management (treatment or new imaging)                             |                       |                     | X  |          |                 |                   |
| Last brain imaging results between 1 week before and 1 week after randomization       |                       |                     |           |          | X        |                   |
| Cerebral Performance Categories (CPC)                                                 |                       |                     |           |          | X        | X          |
| In-hospital infection requiring antibiotics                                           |                       |                     |           |          | X        |                   |
| Use of EEG after intervention                                                         |                       |                     |           |          | X        |                   |
| Need of mechanical ventilation                                                        |                       |                     |           |          | X        |                   |
| Discharge details (date, destination, back to work/school)                            |                       |                     |           |          | X        | X          |

[figure not shown]

## 9.2 Assessments of outcomes

### 9.2.1. Assessment of primary outcome

Mortality at 6 months will be assessed through a structured phone interview (to the patient, representative or general practitioner, depending on the patient's medical condition, consent status and location) by a study team member blinded to the EEG intervention.

### 9.2.2. Assessment of secondary outcomes

The following secondary outcomes will be assessed. Of note, the assessments at 4 weeks will be done through chart review or by phone to the patient, representative or general practitioner, depending on the patient's medical condition, consent status and location. All secondary outcomes at 6 months will be assessed through a structured phone interview (to the patient, representative or general practitioner, depending on the patient's medical condition, consent status and location) by a study team member blinded to the EEG intervention.

- Functional outcome (modified Rankin Scale (mRS), Cerebral Performance Categories (CPC), ordinal), assessed at 4 weeks through chart review or phone and at 6 months through structured phone interview.
- Back to work/school if previously working/at school, assessed at 4 weeks through chart review or phone and at 6 months through structured phone interview.
- Seizure/SE detection rate, and time to detection after the start of EEG recording, and presence of concomitant clinical signs of seizures, assessed through chart review at 48hours.
- Detection of interictal potentially epileptiform features (spikes, spike and waves, sharp waves, isolated or repeated at <3Hz without any evolution; lateralized rhythmic delta activity (proportion)), assessed through chart review at 48hours.
- Rate of in-hospital infections requiring antibiotic treatment assessed at 4 weeks through chart review.
- Need and duration of mechanical ventilation, assessed at 4 weeks through chart review.
- Duration of ICU and hospital stay, assessed at 4 weeks through chart review.
- Patient destination after acute facility, assessed at 4 weeks through chart review or phone and at 6 months through structured phone interview.
- Change in clinical patient management (i.e., AED introduced or stopped, AED increased or decreased, brain imaging procedure order) occurring during the 60 hours following the start of the first EEG (categorical), assessed through chart review at 48-60 hours.
- Correlation between quantitative EEG analysis and outcome assessed, assessed at the study end by the Bern team in a blinded fashion.

### 9.2.3. Assessment of other outcomes of interest

- Global hospitalization costs, intended as amount billed for each patient's acute hospital stay, assessed through the billing department of each hospital, assessed at study end (unblinded).

### 9.2.4. Assessment of safety outcomes

NA

### 9.2.5. Assessments in participants who prematurely stop the study

NA

## 9.3 Procedures at each visit

Study-specific site guidelines detailing screening, consent procedure and data collection for each

study period/timepoint will be prepared prior to study initiation.

#### **Screening and enrolment study period – Day 1 (T-5 to T0)**

This first study “visit” will be dedicated to screening and enrolment of the patient in the trial. Due to the emergency situation this visit will last 5 hours, at maximum. During this visit, evaluation of eligibility, baseline assessments and randomization will be performed. All information for the study outcomes evaluation will be collected from the medical charts.

#### **Intervention study period – Day 1 to Day2/3 (T0 to T48)**

During this study period, the intervention (cEEG or rEEG) will be performed. Concomitant medication (except fluids, vitamins and feeding) and SAE that cannot be excluded to be attributable to the intervention cEEG will also be recorded. All information for the study outcomes evaluation will be collected from the medical charts.

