| Measurements and procedures:           | 
Eligible patients will receive cEEG or rEEG in the first 48 hours following 1:1 randomization.
 
Demographics, etiology, Charlson Comorbidity Index, diagnosis leading to EEG, need and length of mechanical ventilation, and subsequent use of rEEG/cEEG will be prospectively collected. Outcomes will be assessed at 4 weeks and 6 months.
 
Analyses will compare the two interventional groups (intention to monitor, according to intervention allocation) regarding the outcomes. Additionally, lope cross correlation and horizontal visibility graphs will be applied to compute a weighted adjacency matrix consisting of pairwise interdependences between EEG signals, to characterize the integrative and segregative characteristics of the underlying functional brain networks and compare their relationship with the primary outcome.
                                                                                                                                                                                                                                                                                |
| Study Product / Intervention:          | Continuous video-EEG performed once for 30-48 hours.                                                                                                                                                                                                                                                                                                                                                                                                                                                                                                                                                                                                                                                                                                                                                                                                                                                                                                                                                                                                                                                                                                    |

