On the one hand, cEEG has a clearly superior sensitivity in uncovering seizures and SE as compared to routine spot video-EEG (rEEG, which typically lasts 20-30 minutes): a seminal retrospective study in an ICU-based population showed that the detection rate doubles from round 50% after one hour of recording to 95% after 48 hours, especially in comatose subjects. Further evidence for the diagnostic yield of cEEG in patients with altered consciousness comes from a study revealing an increased detection rate of nonconvulsive SE after the introduction of cEEG as compared to historic controls with rEEG (monthly detection rates with cEEG  $5.44 \pm 1.33$ ; with rEEG  $2.17 \pm 1.89$ ,  $p=0.002$ ). Nevertheless, cEEG is a time- and resource consuming procedure, requiring skilled technical personnel, regular assessments by electroencephalographers, and ideally the availability of dedicated, portable video-

EEG recording machines that may be connected to the hospital network for out-of-site inspection, as well as specially conceived supplies allowing emergent imaging procedures (e.g., computed tomography- and magnetic resonance imaging compatible electrodes), namely overnight. Practical considerations have emerged in recent years. For example, it seems that a refined analysis of the first part of cEEG may allow stratifying the risk of encountering seizures in the subsequent recording: if no epileptiform discharge is detected in the first 30-120 minutes, the likelihood would be below 5%. Also, the use of automated software allowing the interpretation of compressed EEG seems to clearly improve efficacy in this setting, reducing the time required to analyze a cEEG by 78%, with minimal loss of sensitivity. While large, mostly academic centers in North America have been using cEEG increasingly since the turning of the century, the vast majority of European hospitals - and all Swiss hospitals including university centers - still do not have the resources to apply cEEG to all patients with consciousness impairment in- or outside the ICUs, and therefore, disturbingly, are not complying with the current European guidelines.

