#### 10.1.1. Definition, assessment and reporting of (serious) adverse events and other safety related events

An Adverse Event (AE) is any untoward medical occurrence in a patient or a clinical investigation participant administered a pharmaceutical product and which does not necessarily have a causal relationship with the study procedure. An AE can therefore be any unfavourable and unintended sign (including an abnormal laboratory finding), symptom, or disease temporally associated with the use of a medicinal (investigational) product, whether or not related to the medicinal (investigational) product (ICH E6 1.2).

As per ClinO Art.63, a Serious Adverse event (SAE) is defined as any event that :

- a. requires inpatient treatment not envisaged in the protocol or extends a current hospital stay;
- b. results in permanent or significant incapacity or disability;
- c. is life-threatening or results in death; or
- d. causes a congenital anomaly or birth defect.

**During the intervention phase of the study, all serious adverse events (SAEs) that cannot be excluded to be attributable to the intervention under investigation, will be collected,** fully investigated and documented in source documents and case report forms (CRF). It is not expected to experience SAE related to the intervention occurring after the intervention.

Additionally, all these events will be reported by the local investigator to the sponsor-coordinating investigator as soon as possible (within 24h). The sponsor-coordinating investigator will report these events to the lead CEC within 15 days (ClinO Art. 63).

If immediate safety and protective measures have to be taken during the conduct of the clinical trial, the local investigator will inform the sponsor-coordinating investigator as soon as possible. The latter will notify the lead CEC of these measures, and of the circumstances necessitating them, within 7 days (ClinO Art.37).

Once a year, the sponsor-coordinating investigator will submit to the lead CEC an annual safety report summarising the safety of participants (ClinO Art.43).

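### The protocol gives conflicting rules on which SAEs are collected and for how long; followed as written, section 9.3 collects them in the cEEG arm only

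*Protocol*

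**What the plan says.** Three parts of the protocol tell sites which SAEs to collect.

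- **Section 9.3, intervention period (T0 to T48).** It first describes the intervention as either cEEG or rEEG. It then states that "SAE that cannot be excluded to be attributable to the intervention cEEG will also be recorded". The Day 3/4 entry (T48 to T60) does not mention SAEs.
- **Section 9.1 flow chart, repeated in the Study Schedule.** The row reads "SAEs potentially related to EEGs". No arm is named, and both the T0–T48 and the T48–T60 columns are marked.
- **Section 10.1.1.** Collection is limited to the intervention phase and covers "all serious adverse events (SAEs) that cannot be excluded to be attributable to the intervention under investigation". Section 2.3 uses the same term for SAE reports to the lead ethics committee.

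The synopsis gives the study intervention as "Continuous video-EEG performed once for 30-48 hours" and lists rEEG separately as the control intervention. Sections 4.4, 5.4 and 9.2.4 set no safety objective, outcome or assessment. Section 11.4.5 plans no safety analysis, and section 1.6 sets up no data safety monitoring committee.

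**The concern.** In a randomised comparison, adverse-event data can be read by arm only if both arms are observed under the same rule. Section 9.3 ties collection to one arm. Under that rule an SAE thought to be linked to a routine EEG has no route into the case report form. The 15-day reports and the annual safety report described in section 10.1.1 could then contain related SAEs from cEEG patients only. A count above zero in one arm against a structural zero in the other looks like a difference in harm when it is only a difference in collection.

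The conflict over the period adds to this. Sites that work from the flow chart would continue to T60, while sites that work from the text would stop at T48. Collection could therefore vary between the five centres as well as between arms.

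**Working it through.** This is a comparison of texts; the plan gives no SAE figure to reproduce.

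**Step 1. The instructions side by side.**

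| Place | EEG to which the SAE must be linked | Period |
|---|---|---|
| 9.3, intervention period | cEEG | T0–T48 |
| 9.3, Day 3/4 | SAEs not listed | T48–T60 |
| 10.1.1 | intervention under investigation (not defined there) | intervention phase |
| 9.1 and Study Schedule | EEGs, no arm named | T0–T48 and T48–T60 |

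**Step 2. What section 10.1.1 means.** Three places point to cEEG. The synopsis lists cEEG as the intervention and rEEG as the control. Section 2.2 uses the same phrase for the procedure that two societies recommend, and section 3.1 shows that this is cEEG. Other places use the word more loosely: sections 8.1 and 9.3 call both procedures interventions. The phrase leans to cEEG but does not settle the matter, so section 10.1.1 cannot decide between the other two texts.

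**Step 3. Is a possibly EEG-related SAE collected?**

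| Patient and time of event | Under 9.3 | Under 10.1.1 | Under 9.1 |
|---|---|---|---|
| cEEG, T0–T48 | yes | yes | yes |
| rEEG, T0–T48 | no | unclear, leans to no | yes |
| cEEG, T48–T60 | no | no | yes |
| rEEG, T48–T60 | no | no | yes |

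The three texts agree only in the first row. Section 10.1.1 does not define the intervention phase in hours; the table takes it as T0–T48, as in section 9.3.

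**Step 4. Size.**

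- Patients affected under section 9.3: 350 planned, allocated 1:1, so 350 / 2 = 175 in the rEEG arm.
- Difference in period: 60 − 48 = 12 hours. If the +24-hour window of the Day 3/4 visit also extends SAE collection (an assumption; the flow chart does not say), it is 12 + 24 = 36 hours.
- Number of SAEs lost: this cannot be derived, because the protocol gives no rate. Sections 3.7 and 10.1 imply that it is close to zero.
- Sample size, alpha and power (174 per arm, 0.05, 0.8 in section 11.2) do not depend on SAE collection and do not change.

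**The case against.** The best defence is that the restriction in section 9.3 is a drafting slip. The sentence just before it names both EEG types, the flow chart sets no arm limit, and section 9.3 promises site guidelines on data collection. Section 10.1.1 also takes its attribution wording from the ordinance it cites, rEEG is standard care, and very few EEG-related SAEs are expected in either arm. This limits the consequence but leaves the conflict in place. Guidelines written from this protocol would still have to choose between its texts.

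A reader might infer more than the document supports:

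- *That risk in the rEEG arm is not monitored.* It is. Six-month mortality is assessed blind in both arms and has an interim look after 100 patients. The mRS and CPC, infections, ventilation, length of stay and 60-hour management changes are also collected in both.
- *That the planning difference in mortality (39% against 25%) measures uncollected harm.* Those deaths are primary-endpoint events and are counted whatever the SAE rule says.
- *That a number of missed seizures in the control arm can be calculated from the statement that "the detection rate doubles from round 50% after one hour of recording to 95% after 48 hours".* This would equate two separate 20–30 minute recordings with one hour of continuous recording. Section 3.4 reports comparable performance of two clipped recordings in 34 postanoxic cases. Linking an SAE to a seizure that nobody observed is debatable in any case.
- *That seizure recording ends too early because week 4 lists only "Use of EEG after intervention".* Section 9.3 collects EEG-related findings to T60, and the cut-off is the same in both arms. A later seizure item would be an additional outcome; its absence does not correct or cause any error.

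**Conclusion.** The contradiction in SAE scope and period is real and should be resolved. Followed literally, section 9.3 gives SAE data from one arm only, and the written rules differ by at least 12 hours. Safety reporting would then be one-sided by construction, and no planned safety analysis or monitoring committee would bring this to light.

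The expected effect is small. It rests on the protocol's own view that EEG-related SAEs are very rare, and on the fact that death and functional outcome are followed in both arms. The claim of one-sided data assumes that sites apply section 9.3 as worded; sites that use the flow chart would collect in both arms. The primary analysis is untouched. The correction is justified because it costs almost nothing and removes an avoidable asymmetry.

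**What to change.** 1. Use one definition in sections 9.1, 9.3 and 10.1.1, and in the reporting text of section 2.3: SAEs for which a link to the allocated study EEG, whether cEEG or rEEG, cannot be ruled out.
2. State one collection period in hours from T0, the same in both arms, and say whether the Day 3/4 visit window extends it. Make the Day 3/4 entry in section 9.3 agree with the flow chart.
3. In section 11.4.5, replace the statement that no safety analysis is planned with a simple tabulation of these SAEs by arm.

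Cost: an amendment to a few sentences, one table, and possibly a few more SAE forms from the control arm. No new visit, outcome or change in sample size is needed.
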